### 6.1.1 Inclusion, determination of max. exercise capacity and familiarization with study protocol (V1)

The purpose of the study will be explained to the patient and informed consent will be obtained. Information on personal details and sport related history will be collected (especially relevant to inclusion criteria). A physical examination which includes basic anthropometric (height, weight, and waist circumference) measurements will be carried out.

Afterwards the maximal physical capacity (VO_2max_) will be determined. The usual therapy will be administered prior to exercise, where appropriate. Subjects will have fasted for at least 6 hours and restrained from strenuous activity for at least 72 hours. VO_2max_ will be determined during an incremental workload test to exhaustion with a brake bicycle Ergometer (CARDIOVIT AT-104 PC Ergo-Spirometrie, Schiller, Baar, Switzerland). The fitness test will be combined with continuous analysis of expired oxygen, carbon dioxide content and minute ventilation using a breath by breath analysis (Oxycon alpha, Jaeger, Würzburg, Germany) and under continuous ECG control.

The patients and sedentary control subjects will begin at a workload of 20 watts, which will be gradually increased by 10-20 watts every minute until exhaustion. The increase in workload is chosen in order to obtain an exercise time of 10-12 minutes in these sedentary subjects. The physically active subjects will begin at a workload of 80 watts.

Afterwards the patients and the sedentary and physically active subjects controls will have a light standardised breakfast before cycling on a treadmill at 50%-55% of VO_2max_ for 90 minutes (= familiarization with the study protocol).

### 6.1.2 Determination of hepatic and skeletal muscle (peripheral) insulin resistance (V2 and V5)

After a fasting blood sampling (GH, IGF-I, cortisol, sex steroids, thyroid hormones, insulin, FFA, glycerol, lipid profile, glucose), a two step hyperinsulinaemic, euglycaemic (5 mmol/L) clamp will be performed (Human Actrapid, Novo Nordisk, Copenhagen, Denmark; low dose insulin: 0.4 mU/kg/min; high dose insulin: 1mU/kg/min) for total 4 hours (each insulin dose 2h). Glucose will be measured every five minutes. Insulin and FFA levels every 15 minutes. Samples for enrichment (glucose) will be taken during the last 30 minutes of each insulin step. The glucose infusion requirements to maintain euglycaemia are recorded. Plasma glucose concentrations are then maintained with an infusion of 20% glucose derived from potato starch, which is recognized to have low ^13^C enrichment. The glucose infusion is spiked with d-[U-^13^C]glucose and d-[6-6-^2^H_2_]glucose to maintain steady enrichment values (hot infusate technique) to avoid dilution of tracer by the glucose infusion (78). Indirect calorimetry will be carried out to assess oxidation rate at baseline and every 30 minutes.

Instructions for a high fat diet will be given at the end of visit 2. This consists of the usual food intake with a supplementary fat intake of 0.75g fat/kg BW, administered as 3 additional snacks per day for three days. A list of suitable fat enriched snacks will be given to the patient. This protocol has previously been shown to efficiently replete IMCL stores (35, 65). A food diary will be kept. The patient will be asked to restrain from physical activity. This will be monitored by a pedometer (Digi-Walker®) throughout the whole period (aim < 5000 paths/24 hours).

Figure 4. Determination of hepatic and skeletal muscle (peripheral) insulin resistance. Tracer and blood sampling schedule

Plasma Insulin, FFA and glycerol concentrations every 15 minutes

Estimated blood volume/clamp: 175 ml

Background enrichment (3x) samples

(air and plasma glucose)

enrichment samples (4x)

(air and plasma glucose)

indirect calorimetry

Plasma glucose measurements every 5-10 minutes

- Tracer Infusion (during clamp with hot infusion technique)
- d-[U-^13^C]glucose 0.8µmol·kg^-1^·h^-1^, primed with 0.6 µmol NaH^13^CO_3_ and 1.2µmol/kg d-[U-^13^C]glucose
- d-[6-6-^2^H_2_]glucose 0.13 µmol/kg/min, primed with 12 µmol/kg

Baseline period (90 min.)

# Low dose insulin

(0.4mU/kg/min) (120min.)

High dose insulin

(1mU/kg/min) (120 min)

0 60 90 180 210 300 330 min

### 6.1.3 Determination of visceral fat mass, repleted and depleted ”ectopic” fat stores, GH-secretion profile (V3 and V6)

The patients will attend the hospital after an overnight fast. After a fasting blood sampling (GH, IGF-I, cortisol, thyroid hormones, insulin, FFA, glycerol, lipid profile, glucose), measurements of total body composition (bioimpedance) and indirect calorimetry, patients and control subjects will receive a conventional standardised breakfast (carbohydrates 50%, Protein 20%, Fat 30%) according to 30% of the necessary energy intake (based on indirect calorimetry). Usual medication will be administered, where appropriate. “Ectopic” fat stores (IMCL, IHCL and whole body fat distribution incl. visceral fat mass will be measured by MRS and MRI, respectively (repleted condition).

Subsequently, patients and control subjects will exercise at 50 % of VO_2max_ for 1.5 hour. Our data (36) and results of the literature (55) suggest that IMCL are already reduced after 1 hour aerobic exercise in sedentary subjects. During the exercise test samples are taken for GH secretion profile (every 15 minutes). IMCL, IHCL and whole body fat distribution will be re-assessed following exercise, (“ectopic” fat stores depleted).

Patients will be instructed in self-administration of GH.

The control subjects will be investigated once.

### 6.1.4 Visits following GHRT (V4-V6)

Usual clinical care will be provided (monthly visit with measurements of body composition (bioimpedance), plasma IGF-I and glucose levels to adjust GH doses in GH-deficient patients. GH dose will be gradually increased in order to obtain IGF-I concentrations in the upper half of the age-adjusted normal range as suggested by the growth hormone research society (76). After six months of GH replacement therapy with a concomitant weight maintaining diet and usual physical activity identical studies will be performed (diet and physical activity matching the first study). V4 corresponds to V1 without familiarization of the study protocol. V5 and V6 matches V2 and V3, respectively.

## 6.2 Details on main experiments

### 6.2.1 Pre-test standardisation and diaries

To control for confounding by external factors relevant to the de- and repletion of lipid stores (such as diet and exercise) detailed diaries will be filled out by patients beginning 1 week in advance of V1 and will be continued until V3. The diaries cover the following items:

- Food ingestion (time, quantity of (at least) carbohydrates, and composition)
- Exercise bouts (Quality, duration, grade, time), pedometer readings

Patients are instructed to eat an isocaloric diet (35-40 kcal/kg body weight; 50-55% carbohydrate, 20% protein, and 20-25% fat). Ingested calories (separated for carbohydrates and lipids) will be calculated from nutrition tables. Strenuous exercise is not allowed 72 h before the test days V1 and V4. Similar activity levels will be monitored by a pedometer (Digi-Walker®) throughout the same period (aim < 5000 paths/24 hours).

### 6.2.2 Resting energy expenditure and body impedance analysis (V2 and V5)

After an overnight fast resting energy expenditure (REE), respiratory exchange ratio (RER), oxygen consumption (VO_2_) and carbon dioxide production (VCO_2_) will be assessed by indirect calorimetry during 20 minutes (DeltatracTM II, AVL Medical Systems AG, Schaffhausen, Switzerland). Rates of substrate oxidation will be calculated using standard equation (79).

Body composition will be estimated by body impedance analysis (BIA 1001/S, RJL systems, Detroit, U.S.A.) after voiding of urine.

### 6.2.3 Exercise test (V1 and V3; V4 and V6)

Each patient will cycle during 90 min at a power which corresponds to 50-55% of VO_2max_ on a cycle ergometer (CARDIOVIT AT-104 PC Ergo-Spirometrie, Schiller, Baar, Switzerland). Patients are asked to pedal with a frequency of 70-90 rpm. Cooling will be performed by fan; the room temperature is kept constant at 20-22°C. There will be no warming up and no encouragement.

- On indirect calorimetry RER, VO2, and VCO2 are measured continuously. Heart Rate is measured continuously with peripheral ECG-leads. At the beginning and at the end of the exercise the patient is asked to empty his bladder. Every 15 minutes RPE is assessed by the Borg scale (by the same investigator).

All procedures will be repeated at the same time of the day and on the same days of the week.

### Clamping (V2 and V5)

The cannula for blood sampling will be placed into a thermo-stabilized box heated at 60°C to achieve partial arterialisation of venous blood. The glucose infusion requirements to maintain euglycaemia (or hyperglycaemia) are recorded. Plasma glucose concentrations are then maintained with an infusion of 20% glucose derived from potato starch, which is recognized to have low ^13^C enrichment. The glucose infusion is with d-[U-^13^C]glucose and d-[6-6-^2^H_2_]glucose to maintain steady enrichment values (hot infusate technique). Glucose will be measured every five minutes (arterialised blood, centrifugated for 3 min at 10.000 rpm, glucose oxidase method in 2300 STAT plus, YSI, Yellow Springs Instruments, Yellow Springs, Ohio, OH).

Regular insulin (Actrapid, Novo Industries, Copenhagen, Denkmark) in isotonic saline is infused in a constant manner with a calibrated volumetric pump (MCM 500, MC Medizintechnik, Alzenau, Germany) at two doses (low dose insulin: 0.4 mU/kg/min; high dose insulin: 1mU/kg/min) The targets for blood glucose levels are set to 5 mmol/L

### 6.2.5 Tracer procedures (V2 and V5)

The following tracers will be administered via calibrated volumetric pumps (MCM 500, MC Medizintechnik, Alzenau, Germany; Harvard 22, Harvard Apparatus, South Natick, MA, USA; Perfusor secura FT, Braun, Sempach, Switzerland) beginning at 8.00 am together with clamping:

- d-[U-^13^C]glucose at a rate of 0.8µmol·kg^-1^·h^-1^, primed with 0.6 µmol NaH^13^CO_3_ and 1.2µmol/kg d-[U-^13^C]glucose (80) to target an enrichment of 0.05%;
- d-[6-6-^2^H_2_]glucose at a rate of 0.13 µmol/kg/min, primed with 12 µmol/kg to target an enrichment of 1.25%;

Baseline blood and breath samples will be taken prior to infusion for measurement of background enrichment. After a 60-min equilibration period to reach steady-state tracer enrichment, the basal steady state will be sampled prior to exercise (-30 to 0 min). The hot infusate technique is used to avoid dilution of tracer by the glucose infusion (81) as described under 6.2.6. All tracers are kindly provided by Prof. [name], CHUV, Lausanne. Isotopes are manufactured by Cambridge Isotope Laboratories, Innerberg, Switzerland.

### Biochemical analysis

Glucose concentrations in plasma will be determined by glucose analyser (Yellow Spring Instruments, Yellow Springs, OH, U.S.A). Plasma FFA and fasting lipid profile will be determined using commercially available kits (FFA: Wako Chemicals, Germany, TG, total cholesterol: enzymatic method Boehringer, Mannheim, Mannheim, Germany; HDL-cholesterol: Wako Chemicals, Germany). These analysis will be performed in the laboratory of Prof. [name], CHUV, Lausanne. Plasma insulin, GH and IGF-I concentrations will be measured by chemiluminescent methods (Immulite^®^). Sex steroids will be determined by solid phase RIA and thyroid hormones will be determined by competitive immunoassay using direct chemiluminescent technology (Chiron Diagnostics, East Walpole, MA, U.S.A). All hormone analysis will be performed in the central chemical laboratory of the Teaching Hospital of Berne (Inselspital) or in the laboratory of [name], Children’s University Hospital of Berne (Inselspital). Serum glucose and lactate is measured by an immobilised glucose-oxidase method (YSI 2300, Yellow Springs Instruments, Yellow Springs, OH, U.S.A.).

### 6.2.7 Mass spectrometry analysis

All isotopic enrichments of glucose and CO_2_ will be determined by gas-chromatography mass-spectrometry (GC 5890/MS 5971, Hewlett-Packard, Palo Alto, CA, U.S.A) in collaboration with the laboratory of Prof. [name], CHUV, Lausanne.

### MRI-Methodology

Magnetic resonance examinations will take place at the MR centre of the Inselspital and University of Bern, performed by the MR section of the Department of Clinical Research (AMSM). MR exams include hepatic (IHCL) and intramyocellular (IMCL) lipid concentrations measured by ^1^H magnetic resonance spectroscopy (^1^H-MRS) and liver volume and whole body fat distribution will be determined by means of magnetic resonance imaging (MRI).

^1^H-MRS before (repleted) and after (depleted) exercise (V2 and V5) will be performed on a clinical 3 T whole body scanner (Magnetom, Trio, Siemens, Germany) equipped with a ^13^C/^1^H double tuned flexible coil (1H: Helmholtz design, Medical Advance). The right leg of a patient will be placed in a specially designed cast to guarantee a reproducible position and shape of vastus intermedius muscle. Positioning of the muscle, fixation of the surface coil, and placement of the ^1^H-voxel will be monitored by two series of localizer images. The same images will be used to calculate total muscle volume. MRS data will be acquired using an optimised press sequence (repetition time = 3 s, echo time = 20 ms, 128 acquisitions, water presaturation, outer volume suppression) and quantified using the unsuppressed fully relaxed MR signal as internal standard. Absolute IMCL levels in mmoles/kg muscle wet weight will be calculated as reported earlier (82). A reproducibility study revealed a typical CV of 6% for repeated measurements (83).

In order to detect potential changes of the liver size and subsequent variations of the total amount of IHCL, liver volume will be determined in end-expiratory breath hold by established MRI sequences that have already been successfully applied by the AMSM (84). In muscle, liver and whole body studies, Cavalieri principles with point counting have been used (84), (85), (86) to determine organ volumes reliably.

Whole body fat distribution incl. visceral fat mass will be determined using the methodology described by Machann J. et al (2005). Briefly, an axial T1-weighted fast spin echo technique with an echo train length of 7 will be applied. Measurements parameters: TE/TR 12 msce/490 msec, slice thickness 10 mm, 5 slices per sequence, 10 mm gap between the slices. The field of view will be 450 mm to 530 depending on the size of the volunteer. A 256 x 178 matrix will be recorded in a measuring time of 12 seconds, allowing breath-hold examinations in abdominal regions. Table shift will be set at 10 cm. Volunteers are in prone position with the arms extended and data are collected from fingers to toes. In total, 100 to 130 images will be obtained depending on the size of the volunteer.

### Calculations

Glucose appearance and disappearance rate will be calculated from d-[6-6-^2^H_2_]glucose, d-[U-^13^C]glucose (internal control) isotopic enrichments, respectively, using Steele’s equations (87) at baseline, after low and high dose of insulin. Glucose oxidation will be calculated from labelled ^13^CO_2_ and labelled d-[U-^13^C]glucose. The volumes of distribution of glucose is assumed to be 100 ml/kg. The bicarbonate pool is assumed to be 14.2 mmol/kg body weight.

## Risk assessment

In this population exercise at the proposed level can be considered safe. The tracer technology using stable isotopes is considered safe with the proposed concentrations. MRI is a non-invasive technology.

## Data management

All subjects’ personal data will be treated confidentially. Only anonymised results will be published or passed on to third parties. Ethics Committee members or Swiss Regulatory Authorities may require to have access to the medical notes of the patients. In this case, these persons will respect the confidentiality of the private data of the study subjects

# Statistical analyses

## Power calculation

There is no data available about IHCL and GH-deficiency. In our previous study (14 GH-deficient patients, 11 control subjects) waist circumference was significantly increased in patients compared to control subjects and significantly decreased (by 2-3 cm) after GHRT suggesting that abdominal fat tissue significantly changes. By including 18 patients we shall have enough power to detect a difference in intraabdominal fat mass. With regard to IHCL the power calculation is,based on IHCL data obtained from patients with type 2 diabetes, which is also an insulin resistant condition (5). . In these patients changes in IHCL were observed after therapy with Rosiglitazone (an insulin sensitizer). It can be estimated that with the paired study design a similar reduction of IHCL (3.6 percent liver mass; SD 4.41, conservatively calculated from *p*-value) would be detected following GHRT with a power of 90% in a sample size of 18 subjects.

## Calculations of the expected effect

Data will be presented as the mean ± SD. Paired t-test will be performed in patients to assess the effect of therapeutical intervention (GHRT). Unpaired t-test will be performed between GH-deficient patients before and after GHRT and control subjects (Atheltes and sedentary controls). In particular ectopic fat depots (i.e. IHCL; IMCL, delta IMCL and visceral fat mass) will be compared before and after GHRT. Unpaired t-test will be used to analyse differences in ectopic fat depots between GH-deficient patients, sedentary control subjects and physically active subjects. Parameters, which are not normally distributed will be log transformed prior to analysis. Alternatively non-parametric tests will be used. Correlation analysis between Ectopic fat depots and measurements of insulin resistance (clamp data) will be performed using Spearman’s rank correlation coefficients. P<0.05 will be considered significant. Statistical analyses will be performed on Stata 9.1 (Stata Corporation, College Station, TX, USA), and Microsoft Excel (Microsoft Corporation, USA).

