# 4. Study population

## 4.1 Patients

Patients with hypopituitarism of the outpatient clinic of the division of Endocrinology and Diabetes of the University of Berne, Inselspital, will be tested for GH-deficiency according to the recommendations of the growth hormone research society (76). A total of 18 patients with adult GH-deficiency will be recruited.

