## 4.4 Control population

Twenty age, gender and BMI matched sedentary (without regular sports activity) subjects will be recruited.

Twenty physically active healthy volunteers will be studied. Criteria for inclusion are: minimum 30’ of exercise 3 times per week and VO_2 max_ > 50 ml O_2_/kg/min for males and >40 O_2_/kg/min for females.

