# 6. Schedule, investigation methods and data acquisition

## 6. 1 General overview (Figure 3)

Figure 3 Clinical Protocol

= equilibrated weight maintaining diet

= minimum 7 days between V1 and V2. no physical activity, equilibrated weight maintaining diet

= minimum 7 days between V2 and V3. High fat diet three days before V3**;** No exercise, food diary.

= usual clinical care: 6 months hypopituitary patients: monthly visits (IGF-I and Bioimpedance measurements)

V1 = Visit 1: determination of VO_2max_ (Spiroergometry). Nutritional advice. Food diary, Familiarization with study protocol (i.e. treadmill)

V2 = Visit 2 Two-step hyperinsulinaemic euglycaemic clamp with stable isotopes (d-[U-^13^C]glucose and d-[6-6-^2^H_2_]glucose)

V3 = Visit 3 MRS/MRI (IMCL, IHCL, visceral fat mass), repleted.

1.5 hour physical activity (bicycle) at VO_2max_ 50-55%, GH secretion profile

MRS/MRI (IMCL, IHCL), depleted

V4 identical to V1 without familiarization

V5 identical to V2

V6 identical to V3

V1

V2

V3

V4

V5

V6

Identical investigations will be performed before and after an intervention. GH-deficient patients will be studied at baseline and after 6 months GH replacement therapy. Sedentary matched control subjects and physically active subjects (road or cross-country cyclists, duathletes, and triathletes; VO_2max_ > 50mL/O_2_/kg) will be tested once.

Investigations include a) determination of exercise capacity (VO_2max_), b) measurements of “ectopic” fat deposition (IMCL, IHLC) and visceral fat mass using MRS and MRI, respectively, in repleted (no physical activity, high fat diet) and depleted (after physical activity) condition. GH secretion profile will be obtained during a standardised exercise. c) hyperinsulinaemic euglycaemic clamp in combination with stable isotope technique and indirect calorimetry to measure hepatic and skeletal muscle insulin resistance and fuel oxidation (77).

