# 9. Time table

Recruitment (including controls) March 2007 – September 2009

Number of GH-deficient patients: 18

Number of controls: 20 sedentary volunteers, 20 physically active healthy subjects

Number of Visits GH-deficient patients: 18x6 = 108

Number of visits sedentary controls: 20x3 = 60

Number of visits physically active subjects: 20x3 = 60

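### Patients are compared with matched sedentary controls and with an unmatched active group by the same unadjusted unpaired t-test: the first contrast loses precision, the second may be confounded by age, sex or BMI

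*Protocol*

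**What the plan says.** Section 4.1 fixes the patient group: "A total of 18 patients with adult GH-deficiency will be recruited". Section 4.4 describes two comparison groups that are selected differently. For the first: "Twenty age, gender and BMI matched sedentary (without regular sports activity) subjects will be recruited". For the second: "Twenty physically active healthy volunteers will be studied", with entry by exercise frequency and sex-specific VO2max limits and no matching. Section 6.1 again attaches the word to one group only: "Sedentary matched control subjects and physically active subjects". Section 9 repeats the numbers: "Number of controls: 20 sedentary volunteers, 20 physically active healthy subjects".

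Section 7.2 then applies one method to both contrasts: "Unpaired t-test will be used to analyse differences in ectopic fat depots between GH-deficient patients, sedentary control subjects" and the physically active group. It extends this to both time points: "Unpaired t-test will be performed between GH-deficient patients before and after GHRT and control subjects". The only alternatives it offers are log transformation and non-parametric tests, and neither uses the matching nor adjusts for age, sex or BMI. The paired t-test is kept for the within-patient effect of GHRT. Section 2.1 names both comparison groups in primary endpoints 1 and 2.

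**The concern.** The protocol names the test, so this is a stated analysis choice and not a detail left to a later plan. The same choice has two different consequences.

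**Patients versus sedentary controls.** Matching makes the groups alike on age, sex and BMI, which removes those factors from the true sampling variation of the difference. The unpaired t-test still counts them in its error term. If they predict a depot, the standard error is too large, the interval too wide and the test less powerful than the data allow.

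**Patients versus active subjects.** Nothing in the selection holds age, sex or BMI equal. Any imbalance in a factor related to a depot goes straight into the estimated difference, and a larger sample would not remove it.

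At stake is how well primary endpoint 1 is answered. Section 7.1 gives no power figure for these between-group contrasts, so their precision has not been budgeted elsewhere.

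**Working it through.** **The plan's own figure.** Section 7.1 gives a paired IHCL change of 3.6, SD 4.41, n = 18 and power 90%. The standardised effect is 3.6/4.41 = 0.816 and the noncentrality is 0.816 × √18 = 3.46. With a critical value of 2.110 on 17 df (two-sided 5%), power is 90.4%. The figure reproduces. It concerns the within-patient change only, which this point does not touch.

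**Inputs for the between-group contrasts.**
- From the protocol: 18 patients (4.1), 20 controls per group (4.4 and 9), significance level 0.05 (7.2).
- Assumed, because the protocol gives no value: a two-sided test; a true difference of 0.8 SD; R² = 0.1, 0.3 or 0.5 for the share of a depot's variance explained by age, sex and BMI; for the active group, a covariate imbalance of 0.5 or 1 SD and a covariate–depot correlation r of 0.3 or 0.5.

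**Matched contrast: interval width.** The standard error factor is √(1/18 + 1/20) = 0.325 SD.
- Unpaired: 36 df, half-width 2.028 × 0.325 = 0.659 SD.
- Adjusted: 38 − 2 − 3 = 33 df, half-width 2.035 × 0.325 × √(1 − R²).

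**Matched contrast: type I error.** With matched groups the true standard error is about 0.325 × √(1 − R²), but the test uses about 0.325. It therefore rejects roughly when |t| on 36 df exceeds 2.028/√(1 − R²), which gives 3.9%, 2.1% and 0.7%. Simulation of matched samples gives the values in the table.

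**Matched contrast: power at 0.8 SD.** Adjusted power uses noncentrality 0.8/(0.325 × √(1 − R²)) = 2.60, 2.94 and 3.48 on 33 df. Unadjusted power has to be simulated on matched samples, because matching already reduces the true variation. The ordinary two-sample formula (noncentrality 0.8/0.325 = 2.46, power 67%) ignores that.

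| Assumed R² | Adjusted half-width (SD) | Unpaired / adjusted | Real type I error, unpaired | Power unpaired | Power adjusted |
|---|---|---|---|---|---|
| 0.1 | 0.627 | 1.05 | 4.0% | 67% | 71% |
| 0.3 | 0.553 | 1.19 | 2.1% | 69% | 82% |
| 0.5 | 0.467 | 1.41 | 0.9% | 72% | 92% |

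The gain in power is about 4, 13 and 20 percentage points. The simulated entries can move by up to about one point, depending on how the two surplus controls are matched. Adjustment narrows the interval once R² exceeds about 0.01.

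**Active contrast: possible bias.** Bias in SD units = r × imbalance. The rejection rate with no true group difference follows from noncentrality bias/0.325 on 36 df.

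| Imbalance (SD) | r | Spurious difference (SD) | Noncentrality | False-positive rate |
|---|---|---|---|---|
| 0.5 | 0.3 | 0.15 | 0.46 | 7.3% |
| 0.5 | 0.5 | 0.25 | 0.77 | 11.6% |
| 1.0 | 0.3 | 0.30 | 0.92 | 14.6% |
| 1.0 | 0.5 | 0.50 | 1.54 | 32.2% |

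With an imbalance of only 0.25 SD, the rate is 5.6% (r = 0.3) to 6.6% (r = 0.5).

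**The case against.** The strongest reply has four parts.

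- **The matched contrast is safe.** Matching has already dealt with bias, and an oversized standard error cannot create false positives. This stands: the cost is efficiency, not validity. With 18 patients and 20 controls, complete 1:1 pairs are impossible, and section 4.4 does not say whether matching is by pair or by group. A paired t-test is therefore not the obvious remedy. On 18 pairs it would narrow the interval only if the within-pair correlation exceeded about 0.12.
- **The sizes are assumed.** This also stands. The protocol does not say how strongly age, sex and BMI predict any depot. One R² need not fit every outcome, and delta IMCL, a within-subject change, may depend on these factors much less than a static depot does.
- **Bias against the active group is not demonstrated.** A reader might infer from the missing matching that this contrast is biased by age and sex. The protocol does not support that, because it gives no age, sex or BMI distribution for the group. Silence on matching permits imbalance but does not establish it. The 32% rate is the top of an assumed range.
- **Adjustment cannot isolate GH status.** The active group differs in fitness by design, and sections 1.2 and 1.3 treat training as itself related to IMCL. This stands and limits what the contrast can mean under any model. It does not justify leaving age and sex uncontrolled as well.

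None of this supplies an adjustment that the protocol lacks, or a reason to prefer the unadjusted test.

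**Conclusion.** The concern holds as a choice of analysis that should be improved. Section 7.2 fixes unadjusted unpaired t-tests for both contrasts of primary endpoint 1, whether or not the comparison group was matched.

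For patients versus sedentary controls the error is conservative. It ranges from slight (about 4 points of power at R² = 0.1) to substantial (about 20 points at R² = 0.5), and is negligible for a depot that the matching factors barely predict. For patients versus active subjects, confounding by age, sex or BMI is possible and uncontrolled, with a false-positive rate of about 7% to 32% over the assumed range.

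A reader might go further and conclude that the trial is underpowered or that its treatment effect is in doubt. The protocol does not support that: the GHRT effect is a within-patient paired comparison, and its stated 90% power reproduces. Confidence is high that the adjustment is absent and that the consequences run in these directions. It is limited for the sizes, which rest on assumed R², correlation and imbalance.

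**What to change.** In section 7.2, replace the between-group unpaired t-tests with a linear model for each depot, on the log scale where needed, containing group (three levels), age, sex and BMI. Report adjusted group differences with 95% confidence intervals. Fit it separately to the patients' values before and after GHRT, so that the two measurements of one patient are not treated as independent.

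For patients versus the active group, adjust for age and sex and show the result with and without BMI, because leanness is partly what distinguishes that group. State that this contrast also reflects the intended fitness difference and so does not isolate GH status.

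The cost is one paragraph and no new measurements. Height and weight are taken at the first visit (section 6.1.1), age and gender are needed for the matching, and sex is needed for the VO2max entry limits. The model spends three degrees of freedom. Where the active group overlaps poorly with the patients in age or BMI, the adjusted difference relies on extrapolation, so the covariate distributions by group should be shown beside it. The paired GHRT analysis and the sample size stay as they are.
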